### Study objectives

2.1

The primary study objectives are to test the correlation between the AF fingerprint, revealing the degree of electropathology including for example, patterns of activation and signal morphology, proteostasis levels and atrial tissue characteristics, clinical characteristics and onset and progression of AF in patients undergoing open‐chest cardiac surgery.

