### Main study parameters and endpoints

2.8

Primary endpoint of the study is development or recurrence of AF. Secondary endpoints include implantation of an atrial pacemaker or implantable cardioverter defibrillator. Additional secondary endpoints are described in the Appendix S1. At present, no substudies are planned.

Deflections of the recorded atrial electrograms are detected semi‐automatically in custom‐made Python 3.6 software. In case of fractionated electrograms, the component with the steepest negative slope is taken as the local activation time (Figure 3). Electrograms with injury potentials and artifacts are excluded from analysis by consensus of two investigators. Signals are used to construct color‐coded activation, conduction block, break‐through wave, fractionation, and voltage maps (Figure 4). Furthermore, the relation between patterns of activation, incidence of breakthrough waves, fractionation, fibrillation intervals, conduction abnormalities, and voltage is studied and compared between the different atrial sites and atrial rhythms. Electrical changes as defined with the above‐mentioned electrical parameters will be correlated with the pre‐operative proteostasis levels, development of post‐operative AF, age, gender, and other clinical characteristics.

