**FIGURE 4 clc23370-fig-0004:**
[figure not shown]
Construction of the atrial fibrillation fingerprint (AFFIP). The left panel shows an example of an activation map during electrically induced atrial fibrillation (AF) of the left pulmonary vein area in a patient undergoing coronary artery bypass grafting without a history of AF. Isochrones are drawn at 5 ms, areas of conduction block (Δ local activation time [LAT] ≥ 12 ms) are indicated by black bars and the origin of peripheral waves by gray dots. The arrows indicate main activation direction. The corresponding fractionation map is displayed in the right panel and shows the different types of atrial potential morphologies: single potentials (SP, one deflection), short double potentials (sDP, two deflections less than 15 ms apart), long double potentials (lDP, two deflections 15 ms or more apart) and complex fractionated potentials (CFP, three or more deflections). The maps are used to determine the incidence of for example, fractionation and conduction block

The primary hypothesis is that the degree of electropathology will be increased in patients with a history of AF and patients whom develop post‐operative AF. Secondarily, we hypothesize that age, gender, underlying heart disease and other clinical characteristics impact the degree of electropathology.

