### Statistical analysis

2.10

Associations between proteostasis markers, electrical signals and clinical patient outcomes are calculated using multivariate logistic regression and cox regression models. Log rank tests compare patient groups with different stages of AF. Continuous and categorical electrophysiological parameters are compared with respectively ANOVA and chi‐square tests. For repeated biomarker measurements, joint modeling and mixed modeling analysis is used. ANOVA with Bonferroni adjustments corrects for analysis of multiple biomarkers.

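### The only stated multiplicity correction is tied to ANOVA, while the marker–AF associations in the primary objective are assigned to regressions with no stated correction

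*Protocol article*

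**What the plan says.** The statistical analysis section (2.10) of the protocol article assigns methods to questions as follows.

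- Markers, electrical signals and outcomes: "Associations between proteostasis markers, electrical signals and clinical patient outcomes are calculated using multivariate logistic regression and cox regression models".
- Repeated marker measurements: "joint modeling and mixed modeling analysis is used".
- Multiplicity: "ANOVA with Bonferroni adjustments corrects for analysis of multiple biomarkers". This is the only multiplicity rule in the article.

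Section 2.8 adds that the "electrical parameters will be correlated with the" pre-operative proteostasis levels, among other variables. It names no test or correction for this.

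Section 2.1 sets the primary aim: "The primary study objectives are to test the correlation between the AF fingerprint, revealing the degree of electropathology". The same sentence goes on to name "proteostasis levels and atrial tissue characteristics, clinical characteristics and onset and progression of AF". Section 2.8 makes new or recurrent AF the primary endpoint. Section 2.7 lists 19 proteostasis markers. A significance level of 0.05 appears only in the sample size section (2.9).

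**The concern.** ANOVA compares mean marker levels between groups. Adjusting those comparisons does nothing to the error rate of a logistic or Cox coefficient. Read literally, the plan lets a marker fail the corrected group comparison and still be reported as associated with AF from a regression that has no stated correction.

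The study aims at a diagnostic tool that predicts onset and early progression of AF, so a false marker could become part of that tool. The Bonferroni sentence could also lead a reader to believe that the error rate over all biomarker claims is controlled, when its stated scope is narrower.

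**Working it through.** **1. Scope of the correction, analysis by analysis**

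| Analysis | Section | Stated correction |
|---|---|---|
| Biomarker ANOVA | 2.10 | Bonferroni |
| Logistic and Cox regression of outcomes on markers and signals | 2.10 | none |
| Joint and mixed models for repeated markers | 2.10 | none |
| Electrical parameters against proteostasis levels | 2.8 | none |

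The second row is the one that relates markers to the primary endpoint.

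**2. The plan's own figure**

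Section 2.9 gives 135 per group, 10% attrition, three groups and a total of 447. Multiplying, 135 × 1.10 = 148.5, rounded up to 149, and 149 × 3 = 447, so the total is reproduced. The 135 cannot be rebuilt because no effect size or SD is given. Assuming a two-group comparison of means, two-sided 0.05 and power 0.95, the implied standardised difference is

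d = √2 × (1.960 + 1.645) / √135 = 0.439.

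This calculation uses 0.05 with no division for multiple markers.

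**3. Chance of at least one false marker**

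Inputs: 19 markers (counted in section 2.7); 0.05 per test (assumed for the regressions); one AF outcome; every marker null; each marker tested separately (assumed).

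- Independent tests: 1 − 0.95^19 = 0.623. Expected false positives: 19 × 0.05 = 0.95.
- Equally correlated test statistics (simulation, 200,000 replicates):

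| Correlation | 0 | 0.3 | 0.5 | 0.7 | 0.8 | 0.9 |
|---|---|---|---|---|---|---|
| Family-wise error | 0.62 | 0.52 | 0.41 | 0.28 | 0.22 | 0.15 |

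The exact count matters little. Under independence, 17 tests give 0.58 and 10 give 0.40.

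**4. What a correction would cost**

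Bonferroni over 19 tests gives 0.05 / 19 = 0.00263 per test. The family-wise error for independent tests is then 1 − (1 − 0.00263)^19 = 0.049.

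Power at d = 0.439 with 135 per group: the expected test statistic is 0.439 × √(135/2) = 3.605, and the two-sided critical value at 0.00263 is about 3.01. Power is Φ(3.605 − 3.01) ≈ 0.72, against the planned 0.95.

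Restoring 0.95 would take 2 × (3.01 + 1.645)² / 0.439² ≈ 225 per group. Allowing for 10% attrition, 225 / 0.9 = 250 per group, or 750 in total.

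**The case against.** The strongest reply is that this reads too much into a five-sentence section of a condensed article. No text says that the regressions are tested at an unadjusted 0.05. The Bonferroni sentence has a broad stated purpose and may be meant to cover more than ANOVA. The full protocol or an analysis plan may define the family of tests. That stands in part: a reader might infer that the regressions are run at full alpha, but the article is silent on their level. The point is confined to what the article does state, which is a correction attached to a different method from the one relating markers to AF. If a wider scope is meant, the sentence needs rewording to say so.

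A second reply is that nineteen separate tests are not specified. Markers could enter a model together, be judged by one overall test, or be combined into the fingerprint. That also stands. The error rates above are conditional on separate tests, and a single decisive global test would remove the problem. The article names no such test.

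A third reply is that the primary hypothesis, at the end of section 2.8, is not about individual markers: "The primary hypothesis is that the degree of electropathology will be increased in patients with a history of AF". This is correct, so the marker tests are only the biomarker part of the primary question. Section 2.1 nevertheless names proteostasis levels in the primary objective.

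Two further inferences are tempting but unsupported. One is that a false marker is likely: at correlation 0.5 or more the chance is below one half. The other is that the marker-by-electrical correlations make false positives nearly certain. That relies on 19 × 6 = 114 tests, with one summary assumed for each of six electrical families, and the article specifies neither the summaries nor pairwise testing.

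**Conclusion.** The concern holds in a limited form: the stated correction and the analyses behind the biomarker part of the primary objective do not match. Its size is conditional. With 19 null markers, separate tests at 0.05 and one AF outcome, the family-wise error is about 0.2 to 0.6 for correlations from 0.8 down to 0, which is roughly 4 to 12 times 0.05. It would be smaller with more strongly correlated markers, and the problem would not arise if one overall test decided. The documents do not establish that the investigators intend uncorrected testing, or that a false marker is more probable than not. This should be settled before the marker analyses are run.

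**What to change.** Reword section 2.10 as follows.

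1. Name one deciding model for the marker associations with the primary endpoint, either logistic or Cox.
2. Apply Holm across all marker terms tested in that model, at family-wise 0.05. Alternatively, make one global test of the markers, or one test of the composite fingerprint, the deciding test.
3. Replace Bonferroni with Holm in the biomarker ANOVA. Holm rejects everything that Bonferroni rejects and sometimes more, so it is never less powerful.
4. Label the marker-by-electrical correlations as exploratory.
5. State that the 0.95 power in section 2.9 applies to a single unadjusted comparison, and use the adjusted alpha to restate power at the recalculation planned after 50 patients per group. On the article's figures (March 20, 2020) that point had not been reached in either AF group: 20 patients had paroxysmal AF and 14 + 2 = 16 had persistent or longstanding persistent AF.

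Cost: the change is to wording and analysis code and needs no new patients or data. The price is statistical. Adjusted P values are less favourable, and per-marker power falls below 0.95, to about 72% in the worst case shown above (plain Bonferroni over 19, a two-group comparison and the implied difference of 0.44 SD). Holm does no worse than that. Keeping 0.95 for each marker would need about 225 evaluable patients per group, so the authors would have to choose between accepting lower per-marker power, enlarging the study and relying on a single global test. A global test avoids dividing alpha but does not by itself show which marker is responsible.

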### Tissue analysis

2.7

All obtained blood samples and atrial tissue samples are stored at ‐80°C until transport to the Amsterdam UMC, location VU Medical Center. Proteostasis markers include HSP27, HSP70, HSPA1A, HSPA5, HSPB1, HSPB5, HSPB6, HSPB7, HSPB8, HSPD1, α‐SMA, LC3B‐II, TIMP1, LOX3, MMP9, Galectin‐3, NCAM, MT‐ND1, and COX3, and are determined by commercially available ELISAs and Western blot analysis at the Department of Physiology of the Amsterdam UMC.

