### Sample size calculation

2.9

Based upon our experience in prior mapping studies approximately 30% of patients develop early post‐operative AF in the Erasmus MC,^13^ which is in correspondence with published literature.^14^

There is no data on the proposed novel electrophysiological parameters and biomarkers, and calculation of the sample size is therefore at present not possible. However, we used data obtained from a pilot study containing five patients with and five patients without AF. With a *P* value of 0.05 and a chosen power of 0.95 the required number is 135 per study group. An attrition rate of 10% increases this to 149 patients in each group. The required sample size for this study is therefore estimated at 447 patients. These calculations will be repeated after the first 50 patients in every group in order to adjust the sample size.

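### Bonferroni for the biomarker ANOVAs is valid, but Holm's step-down procedure gives the same 5% familywise protection with equal or better power: a minor efficiency gain

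*Protocol article*

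**What the plan says.** Section 2.10 (Statistical analysis) fixes the multiplicity method in one sentence: "ANOVA with Bonferroni adjustments corrects for analysis of multiple biomarkers". It names no step-down variant, no family size and no simultaneous confidence intervals.

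Section 2.7 (Tissue analysis) lists the markers: "Proteostasis markers include HSP27, HSP70, HSPA1A, HSPA5, HSPB1, HSPB5, HSPB6, HSPB7, HSPB8, HSPD1, α‐SMA, LC3B‐II, TIMP1, LOX3, MMP9, Galectin‐3, NCAM, MT‐ND1, and COX3". That is ten heat shock protein entries and nine others, 19 in all.

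Section 2.9 (Sample size calculation) uses the unadjusted level: "With a *P* value of 0.05 and a chosen power of 0.95 the required number is 135 per study group". It also says "There is no data on the proposed novel electrophysiological parameters and biomarkers", and it reports no effect size or standard deviation from the pilot.

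**The concern.** Read as single-step Bonferroni, the plan tests each of the 19 markers at 0.05/19, however many of the others have already been rejected. Holm starts at that threshold and relaxes it after each rejection, and it keeps the same familywise guarantee. Where several markers truly differ between the AF groups, the single-step form can miss some that Holm would detect, with nothing gained in error control. At stake is some power in the biomarker comparisons, which feed one side of the study's bio-electrical profile.

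**Working it through.** **Inputs**
- Method: Bonferroni, read as single-step (section 2.10).
- Family size: 19, by counting the list in section 2.7 (inferred).
- Sample size: 135 per group, 149 with attrition, 447 in total (section 2.9).
- Effect size, number of truly different markers and their correlation: not stated, so varied below.

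**The plan's own figure.** The 135 cannot be reproduced without an effect size; it can only be back-solved. For two means with two-sided alpha 0.05 and power 0.95, d = √[2(1.960 + 1.645)²/135] = 0.439. For a three-group ANOVA the same n, alpha and power correspond to f = 0.196. The attrition step agrees: 135 × 1.10 = 148.5, rounded up to 149, and 3 × 149 = 447.

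**Assumed effects.** Two patterns have a largest difference of 0.44 SD, close to the back-solved d:
- A, 0/0.22/0.44 SD: f = 0.22 × √(2/3) = 0.180
- B, 0/0.44/0.44 SD: f = 0.44 × √(2/9) = 0.207

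They bracket f = 0.196.

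**Thresholds.** Bonferroni uses 0.05/19 = 0.00263 for every marker. Holm orders the P values and uses 0.05/19, 0.05/18 = 0.00278, 0.05/17 = 0.00294 and so on, stopping at the first failure. After nine rejections the threshold is 0.05/10 = 0.005.

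**Error control.** Suppose m₀ null hypotheses are true. The first true null that Holm reaches is tested at no more than 0.05/m₀. The chance that any of the m₀ true nulls has a P value that small is at most m₀ × 0.05/m₀ = 0.05, whatever the dependence. Every Holm threshold is at least 0.05/19, so everything Bonferroni rejects is rejected by Holm too.

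**Per-marker power under Bonferroni** (noncentral F, 2 and 402 df, λ = 405f²). At f = 0.196 power is 95% at alpha 0.05 and about 73% at 0.00263. In pattern A, λ = 135 × (0.22² + 0.22²) = 13.07 and power at 0.00263 is about 61%. In pattern B, λ = 17.42 and power is about 80%.

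**Simulated power per true marker at 135 per group, Bonferroni → Holm**

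| True markers | Pattern A | Pattern B | f = 0.196, independent | Extra true markers found (independent) | f = 0.196, correlation 0.5 |
|---|---|---|---|---|---|
| 1 | no gain | no gain | 73.7 → 73.7% | 0.00 | 73.9 → 73.9% |
| 5 | 61 → 63% | 80 → 81–82% | 73.7 → 75.4% | 0.08 | 73.8 → 75.2% |
| 10 | 61 → 65% | 80 → 84% | 73.9 → 78.3% | 0.43 | 73.8 → 77.5% |
| 15 | 61 → 70% | 80 → 87–88% | 73.8 → 82.2% | 1.27 | 73.9 → 80.8% |
| 19 | 61 → 75–76% | 80 → 91–94% | 73.6 → 89.0% | 2.92 | 73.5 → 85.0% |

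Patterns A and B were run as full ANOVAs with correlations 0 and 0.3. The f = 0.196 columns use a chi-square approximation, which explains 73.7% against the exact 73%. A repeat of A and B with correlation 0.5 gave slightly smaller gains: 6–7 points with fifteen true markers and 11–12 with all 19. Holm's familywise error stayed at or below 5% within simulation error.

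**Where the gain shrinks**
- Half the back-solved effect (f = 0.098), 135 per group: at most 2 points in any setting.
- f = 0.196 with 50 per group: 0.8–1.5 points with ten true markers, 2.0–4.5 with all 19.
- Enrolment so far (Table 1: 105 − 36 = 69 without AF, 20 paroxysmal, 14 + 2 = 16 persistent or longstanding): Bonferroni power is only about 5–13% under A and B. Holm adds at most about 1 point with up to ten true markers and 0.2–2.7 points if all 19 differ. The upper end needs pattern B with correlation 0.5.

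**The case against.** The strongest reply is that nothing here is wrong. Bonferroni is valid and standard, and the same suggestion could be made of any plan that names it. That stands, and it is why the point is minor.

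The article is also a condensed text. It does not say single-step, and the sentence could be read to cover pairwise group contrasts as well. Section 2.7 introduces the list with a word that leaves it open, and both blood and tissue are collected, so 19 is an inference. This stands too, but it affects only the size of the gain. Holm is at least as powerful for a family of any size, and the sentence does name multiple biomarkers as what is being corrected for.

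A reader might infer that true markers are being lost for nothing and that the biological part of the fingerprint will be under-reported. The documents do not support that. The larger gains need fifteen or more of the 19 markers to differ. The Introduction describes several failing protein-quality pathways in AF but does not predict how many listed markers will differ across the three groups, and section 2.9 says there are no data on them. Section 2.10 links markers to signals and outcomes through regression models, and nothing says that ANOVA significance decides what enters the fingerprint. Single-step Bonferroni also has one real convenience, simple simultaneous intervals, although the article plans none.

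**Conclusion.** The point holds as a minor efficiency improvement. That Holm is never less powerful at the same familywise error is a mathematical result and needs no assumption about the markers. The size of the benefit does. With 19 markers, 135 per group and the assumed shifts, it is 0 points with one true marker, about 1–2 with five, about 4 with ten, about 7–9 with fifteen and about 11–15 only if all 19 differ. It is smaller with weaker effects and close to nil at present enrolment unless nearly all markers differ. Even in the best case Holm recovers only part of the fall from 95% to about 73% power that the adjusted level brings at the back-solved effect.

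**What to change.** In section 2.10, replace the Bonferroni wording with: *Holm's step-down adjustment across the biomarker family at familywise alpha 0.05*.

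This is a change of one phrase. It needs no patients, data or new assumptions, and it cannot reduce the number of markers declared different. If simultaneous confidence intervals are wanted, Bonferroni intervals can be shown beside the Holm-adjusted P values. Some markers may then be significant by Holm while their Bonferroni interval includes no difference, which a footnote can explain.

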## RESULTS

3

The AFFIP study started in January 2017. The first patient enrolled on January 27, 2017, and up till now 105 patients were included (as of March 20, 2020), of whom 36 have a history of AF. Table 1 provides the preliminary baseline characteristics of all enrolled patients.

**TABLE 1 clc23370-tbl-0001:** Preliminary baseline characteristics of enrolled patients (as of March 20, 2020)

Number of patients	105
Male	70 (67%)
Age (years)	64 (54‐71)
BMI	27.2 (24.6‐30.1)
Underlying heart disease	
CABG	16 (15)
AVD	18 (16)
MVD	11 (10)
CABG + AVD	8 (8)
CABG + MVD	4 (4)
AVD + MVD	4 (4)
CHD	44 (42)
History of AF	36 (34)
Paroxysmal	20 (56)
Persistent	14 (39)
Longstanding persistent	2 (6)
Hypertension	48 (46)
Dyslipidemia	26 (25)
Diabetes mellitus	16 (15)

*Note:* Values are presented as N (%) or median (25th to 75th percentile).

Abbreviations: AVD, aortic valve disease; BMI, body mass index; CABG, coronary artery bypass grafting; CHD, congenital heart disease; MVD, mitral valve disease.

## DISCUSSION

4

In clinical practice, AF is currently diagnosed with a surface electrocardiogram when a patient already suffers from AF. This rhythm registration cannot assess the degree of electropathology and thus the stage of AF which is essential for selection of the appropriate therapy. Hence, early recognition of AF and the start of effective treatment is seriously hampered. The AFFIP study aims to characterize electropathology, enabling development of a novel diagnostic instrument to predict AF onset and early progression. Electrophysiological data obtained from epicardial mapping during surgery are combined with proteostasis markers on one hand and atrial tissue characteristics on the other hand. The findings will elucidate whether electrophysiological and structural characteristics represent a novel diagnostic tool, the AF fingerprint, to predict onset and early progression of AF in patients who had cardiac surgery.
